#### 4.4 Exit from the trial

A participant or his/her surrogate is free to withdraw from the trial at any time. A participant will exit the trial if the participant withdraws her/his consent. The participant making the withdrawal of consent will be asked for permission to use the data acquired up to that time point and if data for the primary endpoint can be collected. If permission is obtained, the participant will be included in the final analyses. If the participant declines, all data with the exception of initials, sex and date of withdrawal will be destroyed. If the trial intervention is discontinued by the treating physician because of adverse events, if the participant is withdrawn from active care and/or the focus of care is changed to palliation, or any other reason, this does not constitute withdrawal from the trial and the participant will not exit the trial (data collection will continue). A participant transferred to a non-REDUSE ICU will not exit the trial. All participants randomized in this trial will be analysed on an intention-to-treat basis.

### 5. Trial design

The trial is a multicentre, randomized trial with a 1:1 concealed allocation. Participants will receive either protocolized restrictive administration of non-resuscitation fluids or usual care. The trial will be investigator-initiated and non-commercial. The steering group, author group, trial statistician, outcome assessors, prognosticators and the trial coordinating team will be blinded to group allocation. Please see Table 1 for a study schedule.

#### 5.1 Screening and randomisation

Clinical investigators at each participating ICU will be responsible for screening of all admitted patients with a diagnosis of septic shock. A screening log will be compiled while the trial is active at each site and will include all adult patients with an admission diagnosis of septic shock whether they are eligible for inclusion or not. We will document reasons for not including an eligible patient. Informed consent will be obtained as specified in each national ethical approval. Trial sites will have access to an internet-based randomization application within the eCRF to allow for immediate allocation and adequate generation and concealment of the allocation sequence. Each patient will be assigned a unique trial number. Randomization will be performed with permuted blocks of varying block size unknown to the trial investigators, stratified for trial site.

#### 5.2 Intervention

Participants will receive non-resuscitation fluids according to the protocol described below within two hours of randomization. Non-resuscitation fluids are defined as fluids other than colloids, blood products, or crystalloids administered to correct hemodynamic impairment as noted in the participants' charts. The type of maintenance fluids will be given according to usual care at each respective centre with the objective to use similar types of fluids in both groups. The allocated treatment will be continued while the participant is admitted in an ICU participating in the REDUSE trial up to a maximum of 90 days. Patients readmitted to an ICU

participating in the REDUSE trial within 90 days of inclusion will receive the same treatment to which they were initially allocated regardless of admission diagnosis.

### 5.2.1 The intervention group

- Maintenance fluids will be discontinued in participants with a positive cumulative fluid balance who are judged not to be dehydrated by the treating physician.
- Glucose may be used at a maximal dose of 1g/kg/day using 20% or more concentrated glucose solutions starting at 72 h after inclusion as nutrition if enteral feeding is not tolerated. Glucose at this concentration or higher may be started earlier in patients at risk of hypoglycaemia (blood glucose <5 mmol/l and trending downwards) and in patients with insulin dependent diabetes if enteral feeding is not tolerated and if mandated by local protocol.
- Intravenous medications will be concentrated according to a trial specific protocol (Appendix D).
- Enteral nutrition will have an energy density of 2 kcal/ml and administered according to local protocols.
- Participants with neutral or negative cumulative fluid balance will receive maintenance fluids and other fluids such that the total dose covers their daily water need (about 1ml/kg/h).
- Intravenous fluid and enteral water will be used to correct electrolyte disturbances as needed.
- Parenteral nutrition will be given according to local protocol.

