##### 5.5.3. Protocol deviations

Protocol deviations include randomization of a non-eligible patient and non-compliance with treatment algorithm in the intervention and control arms as described above.

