#### Daily from day 1 - 5 after inclusion

- Patient in a REDUSE ICU this day (Y/N)
- Resuscitation fluids (Crystalloids administered to correct hemodynamic impairment as noted in the patient chart or given at a rate > 5 ml/kg/h (Ringer's acetate/lactate [ml], 0.9% NaCl [ml], other [ml]; Colloids (Albumin 4-5% [ml], Albumin 20% [ml], other [ml]; Blood products (Erythrocytes [ml], Plasma [ml], Platelets [ml])).
- Intravenous vehicles and drugs (Antibiotics [mL], Inotropes (includes dobutamine, levosimendan, or dopamine <5mcg/kg/min) [mL], Vasopressors [mL], Analgesics [mL], Sedatives [mL], Insulin [mL] and dose [E/24h; If the patient was in the ICU for less than 24 hours this day, extrapolate the dose to 24 hours], Potassium [mL], Other electrolytes [mL], Other drugs [mL], 5% glucose used as a vehicle [mL], Other concentration of glucose used as a vehicle [mL and concentration in %]).
- Maintenance/replacement and nutrition (Crystalloids administered for reasons other than correcting hemodynamic impairment. If indication in the medical charts is unclear, crystalloids at a rate below 5 ml/kg/h will be classified as maintenance fluids (Ringer's acetate/lactate [ml], 0.9% NaCl [ml], other (ml)), Glucose (2.5% [ml], 5% [ml], 10% [ml], 20% (ml), other glucose strength (mL and concentration in %)), was no or 20% glucose given in accordance with established local protocols/routines; Parenteral nutrition (ml); Enteral nutrition (ml); Enteral water (ml); Other fluids (mL); Total caloric intake [including Propofol and glucose solutions] (kcal)
- Diuretics (Loop diuretics/furosemide [mg/24h], Other (type of drug and mg/24h)
- Fluid output (Urinary output [ml], Drains [ml], Haemorrhage [ml], Faeces [if liquid and collected through a faecal management system, ml], Fluid removal in RRT [ml], Other losses [evaporation excluded] (ml)
- Fluid balance (Total fluids that day [mL], Fluid balance [mL], Cumulative fluid balance [mL], Total volume of resuscitation fluids [mL], Total volume of non-resuscitation fluids [mL], Weight [kg], Fluid balance goal for next 24h [Y/N, and volume in mL])
- Creatinine [highest](μmol/L)
- Acute Kidney Injury (Calculated based on creatinine and urine output [Y/N], if yes specify KDIGO score)
- Renal replacement therapy (Y/N)
- Earliest urea (mmol/L; Value closest in time to the change of day at the institution.)
- Lowest MAP (mmHg; Lowest value that day)

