- Type of inotropic drug or vasopressor (any dose of dobutamine, dopamine, vasopressin or other V1A agonists, levosimendan, angiotensin II, noradrenaline, adrenaline, milrinone, or other)
- Noradrenaline dose (highest dose during the day;  $\mu\text{g/kg/min}$ )
- Corticosteroid treatment (Y/N)
- Atrial fibrillation/flutter (Y/N)
- Mechanical ventilation (Y/N)
- Lowest PaO2 (kPa)
- FiO2 (at time of lowest PaO2; %)
- Lactate [highest] (mmol/L)
- Sodium [earliest] (mmol/L)
- Potassium [earliest] (mmol/L)
- Chloride [earliest] (mmol/L)
- Blood glucose [earliest] (mmol/L)
- Ischemic events (Y/N) (criteria described above), if yes, specify: a) Limb, b) Cerebral, c) Heart, d) Intestine
- Hypoglycemia (Mild/moderate hypoglycaemia 2.3 - 3.9 mmol/L) (Y/N), Severe hypoglycaemia  $\leq 2.2$  mmol/L) (Y/N)
  - o If yes to severe hypoglycemia:
    - Was the patient receiving IV glucose at the time of the event (Y/N)
    - Was the patient receiving insulin at the time of the event? (Y/N)
    - Was the patient receiving enteral nutrition at the time of the event (Y/N)
    - Additional information/details (free text)
- Hypernatremia [ $>159$  mmol/L] (Y/N)
- Hyperchloremic acidosis [ $\text{pH}<7.15$  and plasma-chloride  $>115$  mmol/L] (Y/N)
- Metabolic alkalosis [ $\text{pH}>7.59$  and base excess  $>9$ ] (Y/N)
- Central venous catheter complications (Includes malfunctions, infections, thrombosis and venous stenosis) (Y/N and specify)
- Suspected unexpected adverse events (SUSAE) (Y/N); (A SUSAE is an adverse event not reasonably explained by other factors than the intervention which may cause death, be life threatening, prolong hospitalisation, or result in significant disability/incapacity.)

Daily from day 6 to discharge from REDUSE ICU or day 90

- Patient in a REDUSE ICU this day (Y/N)
- Fluids (Total volume of resuscitation fluids [mL], Total volume of non-resuscitation fluids [mL], Total fluid output [mL], Fluid balance[mL])
- Ischemic events (Y/N) (criteria described above), if yes, specify: if yes, specify: a) Limb, b) Cerebral, c) Heart, d) Intestine
- Any new Acute kidney injury (Y/N, if yes specify KDIGO score [1-3])
- Hypoglycemia (Mild/moderate hypoglycaemia 2.3 - 3.9 mmol/L) (Y/N), Severe hypoglycaemia  $\leq 2.2$  mmol/L) (Y/N)
- Hypernatremia [ $>159$  mmol/L] (Y/N)
- Hyperchloremic acidosis [ $\text{pH}<7.15$  and plasma-chloride  $>115$  mmol/L] (Y/N)

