### TREATMENT ALGORITHM FOR NON-RESUSCITATION FLUIDS – INTERVENTION ARM

Enteral nutrition: 2 kcal/ml, start according to local protocol.  
 Glucose solutions: 20% or higher concentration a).  
 Parenteral nutrition: according to local protocol.  
 Intravenous fluid and enteral water: given as needed to correct electrolyte disturbances, according to local protocol.  
 Medications and electrolytes: administer according to separate protocol.  
 Maintenance fluid: see flow chart below.

[figure not shown]

a) Administer ONLY in patients where enteral nutrition is not tolerated, earliest start 72 hrs after randomization. Maximum dose 1g/kg/day. Glucose solutions can be used earlier in patients at risk for hypoglycaemia (blood glucose < 5 mmol/l and trending downward).

b) Measured ins and outs:

Ins: nutrition, maintenance fluids, medications and electrolytes, blood transfusions, colloids.

Outs: diuresis, fluid removal from renal replacement therapy, tube drainage, vomiting/gastric tube drainage, bleeding, contents from faecal management system.

c) Overhydrated (increased total body water relative baseline) as suggested by weight above baseline/preadmission body weight, and/or peripheral/radiological oedema

d) Dehydrated (decreased total body water relative baseline) as suggested by body weight below baseline/preadmission body weight, decreased skin turgor and/or dry mucus membranes.

e) Maintenance fluid: intravenous fluid or enteral water prescribed to ensure that total volume of fluid covers basic need of water (approx 1 ml/kg/h).

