# Appendix D. Medications in the intervention group.

The concentrated solutions should only be used once the patient has a central line. To avoid waste of drug, apply protocol when it's time to change syringe. Glucose may also be supplied as a vehicle for medication rather than a separate infusion of 20% glucose in patients receiving glucose for the indications described in the treatment algorithm (Appendix C). More concentrated solutions and higher infusion rates than those described below are allowed if already in use at trial site. Drugs not included in the table below should be used in the most concentrated dilution already in use at trial site.

| Drug                                                               | Conc. in stem solution | Suggested dilution in intervention group                                                                                 | Reference                                   | Comments                                                                                                                                                      |
|--------------------------------------------------------------------|------------------------|--------------------------------------------------------------------------------------------------------------------------|---------------------------------------------|---------------------------------------------------------------------------------------------------------------------------------------------------------------|
| Suggested dilutions may only be used if patient has a central line |                        |                                                                                                                          |                                             |                                                                                                                                                               |
| Vasoactive drugs                                                   |                        |                                                                                                                          |                                             |                                                                                                                                                               |

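### Appendix C footnote a) leaves out the early-glucose exception for insulin-dependent diabetes that section 5.2.1 grants, so two live treatment instructions conflict

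*Protocol*

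**What the plan says.** Protocol section 5.2.1 permits glucose of 20% or more as nutrition from 72 h after inclusion if enteral feeding is not tolerated, up to 1 g/kg/day. It then allows an earlier start in two groups. The first is patients at risk of hypoglycaemia, defined as blood glucose below 5 mmol/l and trending downwards. The second is added in the same sentence: "and in patients with insulin dependent diabetes if enteral feeding is not tolerated and if mandated by local protocol".

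Appendix C is the treatment algorithm for the intervention arm. Its footnote a), attached to the glucose line, reads "Administer ONLY in patients where enteral nutrition is not tolerated, earliest start 72 hrs after randomization". After the dose cap it gives one exception: "Glucose solutions can be used earlier in patients at risk for hypoglycaemia", with the same 5 mmol/l threshold. Diabetes is not mentioned. A separate line of the algorithm leaves another route open: "Parenteral nutrition: according to local protocol".

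Appendix D, the medication list, allows glucose as a drug vehicle in place of a separate 20% infusion "in patients receiving glucose for the indications described in the treatment algorithm (Appendix C"). Its indications thus come from the algorithm and not from section 5.2.1.

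**The concern.** The two texts instruct the same staff about the same patients in the same arm, and they differ. Section 5.2.1 deliberately exempts insulin-dependent patients whose unit mandates glucose when they cannot be fed enterally. The algorithm, in its legible text, removes that exemption. The protocol has no rule saying which text prevails.

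At stake is consistent and safe delivery of the intervention. Under section 5.2.2, usual-care patients receive non-resuscitation fluids by local routine, so they would receive glucose that the local protocol mandates. Intervention patients treated by footnote a) might not, although section 5.2.1 does not intend that difference. A site working from section 5.2.1 and a site working from the sheet could also treat the same patient differently.

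**Working it through.** No arithmetic applies. The check is a comparison of the texts, rule by rule.

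1. **Routine start.** Section 5.2.1: 72 h after inclusion. Footnote a): 72 h after randomisation. Section 10 counts patients as included when they are randomised, so these are the same time point and agree.
2. **Condition for routine use.** Both require that enteral feeding is not tolerated. Agree.
3. **Maximum dose.** Both 1 g/kg/day. Agree.
4. **Concentration.** Both 20% or more. Agree.
5. **Early start for hypoglycaemia risk.** Both below 5 mmol/l and falling. Agree.
6. **Early start for insulin-dependent diabetes** (enteral feeding not tolerated, local mandate). Present in section 5.2.1, absent from footnote a). **Conflict.**

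Section 5.2.1 therefore has two early-start exceptions and footnote a) has one.

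**Does the hypoglycaemia exception already cover these patients?** Take an insulin-dependent patient before 72 h who does not tolerate enteral feeding, in a unit whose protocol mandates glucose. There are four possible states of blood glucose:

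- below 5 mmol/l and falling: permitted by both texts;
- below 5 mmol/l and not falling: permitted by section 5.2.1 only;
- 5 mmol/l or more and falling: permitted by section 5.2.1 only;
- 5 mmol/l or more and not falling: permitted by section 5.2.1 only.

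The texts agree in one state and differ in three. If the first exception covered every such patient, the second would have no purpose in section 5.2.1.

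**Could footnote a) be shorthand?** The word ONLY, a stated earliest time and one named exception make a closed list. A reader holding only the sheet has no sign that a further exception exists.

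**Could the figures that are not shown cure it?** Two figures in Appendix C are not visible. The text assigns the flow chart to the maintenance-fluid line; the content of the figure under the appendix heading is unknown. Footnote a) is fully legible. If a figure did show the diabetes exception, Appendix C would contradict its own footnote and the same correction would be needed.

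**Appendix D.** Because it refers to the algorithm for its glucose indications, it carries the narrower list. This is a consequence of the one omission and not a second error.

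**The case against.** The strongest reply is that the operative text is section 5.2.1. Section 5.2 says participants are treated by the protocol that follows it, and section 5.2.1 cites Appendix D but not Appendix C. The exception is permissive, and it applies only where a unit already has its own standing instruction to give glucose. The eCRF also reminds sites of local routine on each of days 1 to 5 by asking "was no or 20% glucose given in accordance with established local protocols/routines". Parenteral nutrition by local protocol, the hypoglycaemia exception and 5% glucose as a drug diluent all remain available under the appendices.

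Much of this stands. A reader might infer that staff *would* withhold the glucose. The documents support only that they *could*, since that depends on which text they work from. The eCRF item, however, records what was given; it does not authorise treatment that the algorithm rules out.

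Three further inferences are tempting and not supported.

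- **Severe hypoglycaemia.** After a severe event the eCRF asks "Was the patient receiving IV glucose at the time of the event (Y/N", with companion questions on insulin and enteral nutrition, and the DSMC reviews severe hypoglycaemia. One might read these items as aimed at this subgroup. They are asked after any severe event and do not mention diabetes. Severe means 2.2 mmol/l or lower, whereas footnote a) already opens early glucose below 5 mmol/l and falling, so a patient heading for a severe event would normally meet the existing exception first.
- **Per-protocol set.** Section 5.5.3 counts as a deviation "non-compliance with treatment algorithm in the intervention and control arms as described above". One might conclude that early glucose given under section 5.2.1 would be logged as a deviation and the patient dropped from the per-protocol population. The closing reference to what stands above points most naturally to sections 5.2.1 and 5.2.2, where the glucose is allowed.
- **Amount of glucose lost.** Multiplying the daily cap over the first 72 h gives only a ceiling. It assumes that the cap applies to early glucose, that glucose would start at once and that the full dose would be given. It is not an expected loss.

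**Conclusion.** The contradiction holds. It is an internal inconsistency in a live treatment instruction, not a fault in the design or the statistics. Footnote a), and Appendix D through it, omit one of the two early-start exceptions in section 5.2.1.

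The gap is narrow. A patient is affected only if all of these hold before 72 h: insulin-dependent diabetes, enteral feeding not tolerated, a local protocol that mandates glucose, and blood glucose not both below 5 mmol/l and falling. The protocol gives no rate for any of them, so the number affected is unknown. The harm is limited to the possibility that permitted and locally mandated glucose is withheld by staff who rely on the sheet. No effect on the intention-to-treat analysis, the per-protocol set, the sample size or the power is shown.

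The conclusion assumes that section 5.2.1 states the intended rule and that staff may use the algorithm sheet without it. The correction is worth making because it is cheap and restores an exemption that the main text grants on purpose.

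**What to change.** In Appendix C footnote a), extend the sentence on earlier use so that, after the hypoglycaemia exception, it carries the clause from section 5.2.1: "and in patients with insulin dependent diabetes if enteral feeding is not tolerated and if mandated by local protocol". Reissue the algorithm sheet to all sites. Appendix D needs no edit, because it follows Appendix C by reference, and section 5.5.3 needs none either.

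The cost is one clause and one reissued sheet. The eCRF, outcomes, sample size and analysis stay as they are.

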### 5.2.2 Usual Care group

- Non-resuscitation fluids will be administered according to local routines.
- Unless the local protocols dictates otherwise, maintenance fluids (enteral water, crystalloids and/or glucose) will be given at 1 ml/kg/h.
- Unless local protocol dictates otherwise, a maximum glucose concentration of 10% will be used.
- Medications will be concentrated according to local protocol.

Site investigators will establish what constitutes usual care in their ICU prior to initiation of the trial. Site investigators will ensure protocol adherence in the two groups through continuous treatment monitoring.

Resuscitation fluids (albumin, blood products, crystalloids given to correct hemodynamic impairment as noted in patient chart or at a rate of  $\geq 5$  ml/kg/h if indication is unclear) will be administered according to local protocol (Finfer 2010). All other care will be according to local routines and not protocolized.

## 5.3 Follow up

At 6 months, a specially trained and blinded outcome assessor will perform a structured telephone interview and administer the MoCA-BLIND, EQ-5D-5L, GOSE, WHODAS and MFIS

evaluations. In cases where the participant's outcome is too poor to complete the tests, a relative or close friend will be asked to rate the participant's HRQoL by the EQ-5D-5L test. The outcome assessor may be an occupational therapist, a physician, a research nurse, or a psychologist. Outcome assessors will receive a trial manual with detailed guidelines for performing the questionnaires and assessments. Training sessions will be provided by the trial coordinating team. To avoid missing data alternative strategies will be used. These include inviting the participant to visit a clinic, visiting the participants' home or an audio-visual web-based meeting. If needed an authorized interpreter will be used.

#### 5.4 Blinding

The clinical team caring for participants bedside and the research staff collection data up to 90 days after inclusion will not be blinded due to the nature of the intervention. The participants and their family will not be informed about group allocation. The steering group, author group, trial statisticians, outcome assessors at 6 months and at one year, the trial coordinating team, manuscript writers and the data safety and monitoring committee will be blinded to group allocation. The two groups will be coded as "A" and "B". Two conclusions from all outcomes in the main manuscript will be drawn: one assuming "A" is the intervention group and "B" is the control group - and one assuming the opposite. All conclusions must be approved by the author group before the code is broken.

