## 2.4 Rationale for a new trial

Based on data showing that non-resuscitation fluids are the major source of fluid after the first day in the ICU we recently performed a feasibility trial comparing a protocolized reduction of non-resuscitation fluids to usual care in septic shock (Lindén-Søndersø 2019, Lindén 2023, Linden 2024). Our data shows that this approach may reduce the total volume of administered fluids by a median of 3.6 (95% CI; 1.6 to 5.3) L in the first 3 days after inclusion. This reduction is almost twice as large as the most effective protocol targeting the restriction of resuscitation fluids (Meyhoff 2022) and could potentially impact outcomes. In addition, it is unknown whether the balance between benefits and harms of resuscitation fluids differs from that of non-resuscitation fluids. Taken together, a trial powered to detect if restrictive administration of non-resuscitation fluids influences patient-important outcomes is warranted.

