### 6.1 Quality control of data

Site principal investigators will be responsible for training clinical staff on correctly entering variables into the electronic case report forms (eCRFs). Particular emphasis will be placed on recording fluid administration and fluid balance data in a standardized manner. Instructions will be available in the trial master file and eCRFs. All sites will receive a site initiation visit via a digital meeting from an independent monitor before the start of inclusion. Moreover, monitors will visit all sites when 10 participants have been included. The visits will include control of routines for data collection and entry as well as quality control of data by source data verification. To minimize missing data and ensure adherence to the protocol we will use central monitoring and we will develop a central monitoring plan before the start of the trial. The site investigator must sign all eCRFs before trial completion to verify that the recorded data is correct and complete.

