#### 10.4 Exploratory analyses

We will perform an analysis including only centres in which a median difference in total volume of administered fluid between the groups is  $> 3$  L at day 4. We will also perform a subgroup analysis including only centres in which the median difference in cumulative fluid balance is  $> 2$  L at day 4. Because patients staying longer in the ICU will be exposed to the intervention for a longer time we will perform a subgroup analysis of patients staying four days or more in the ICU. Because the amount of glucose may differ between the intervention- and control group we will also perform an analysis of the interaction between the amount of intravenous glucose prior to full enteral nutrition or initiation of parenteral nutrition and treatment effect.

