## 11. Publication of Data

The analysis process will be performed with the allocation code unbroken and with the trial arms only known as A and B. Two abstracts of the main publication will be prepared before the allocation code is broken, with the different arms interchanged (one assuming arm A is the intervention arm, and the other assuming arm B is the intervention arm). All authors must approve both versions before the code is broken. The final main publication will be submitted to a peer-reviewed international journal. Authorship will be granted using the Vancouver definitions and depending on personal involvement and fulfilment of the authors' respective roles. The author list will include the steering group members, national investigators and additional names. Centres recruiting >30 participants will be entitled to one name, >60 two names, >100 three names, >150 four names, >220 five names in the author list (additional names). After the author list, there will be added: "and the REDUSE-trial group" and a reference to an appendix with all sites, site investigators and the number of participants enrolled. The main publication will report the primary and secondary outcomes. Exploratory outcomes will, due to complexity of reporting be submitted to a peer-reviewed journal in separate manuscripts, as will the studies based on the biobank. Ideas for additional substudies will be presented to the steering group. The steering group will decide which substudies to prioritize. No substudy will be published prior to publication of the main article.

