### 15.2 Steering group

All principal site investigators will be part of the steering group. A representative from the newly formed patient organisation "Sepsisföreningen" will be invited to the management group meetings if/when aspects of the conduct of the trial which are deemed to be of importance from a patient perspective are discussed. Such aspects include any change in the protocol with ethical implications.

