### 6. Communication between the steering group and the DSMC

The DSMC will be blinded in its safety and efficacy data assessments. Data transferred to the DSMC will be aggregated according to treatment group and labelled as group A and group B. The DSMC can request unblinding from the steering group. The data transferred from the steering group to the DSMC will be prepared by an independent liaison, with assistance from the trial statistician, in a manner that allows all trial personnel to remain blinded.

The DSMC can request additional reports concerning outcome measures and complications at any time during the trial. The reports should be up-to date should be provided to DSMC within 1 week of the request.

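### The steering group and authors are called blinded to allocation, but members with a site role know it for their own patients; they can be blind only to pooled results by arm and to the A/B code

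*Protocol*

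**What the plan says.** - **Who is blinded.** Protocol section 5.4 names "The steering group, author group, trial statisticians, outcome assessors at 6 months and at one year, the trial coordinating team", followed by the manuscript writers and the DSMC, as blinded to allocation. Section 5 also names the steering group and author group, and section 1 names the manuscript authors. None of these statements is qualified. Section 5.4 says that bedside teams and research staff collecting data to day 90 are not blinded.
- **Who sits on these bodies.** Section 15.2: "All principal site investigators will be part of the steering group". Section 11 puts the steering group members on the author list.
- **What site investigators do.** Section 5.2.2: "Site investigators will ensure protocol adherence in the two groups through continuous treatment monitoring". Section 9.2 has them assess whether a suspected unexpected serious adverse event (SUSAE) was caused by the intervention.
- **The A/B procedure.** Section 11: "The analysis process will be performed with the allocation code unbroken and with the trial arms only known as A and B". Two opposite versions are approved by all authors before the code is broken.
- **Unblinding route.** Appendix B section 6: "The DSMC can request unblinding from the steering group". Under Appendix B section 8 the same group decides whether to continue, hold or stop, and accepts or rejects proposed amendments. Under section 9 the DSMC may suggest a change in sample size.
- **Data that differ by arm.** Section 10.4 (exploratory analyses) plans an analysis "including only centres in which a median difference in total volume of administered fluid between the groups is" above 3 L at day 4. Section 10 defines a per-protocol set from deviations that section 5.5.3 judges against each arm's own rules. Section 6.1 adds: "To minimize missing data and ensure adherence to the protocol we will use central monitoring".

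**The concern.** Care in this trial is open, so the declared protection against biased conduct and interpretation is that the people who steer the trial and write its conclusions do not know the allocation. If that statement is untrue for many of them, the publication will repeat a claim that the design does not support.

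Two practical consequences follow. A DSMC that wants the code has to tell the steering group so, and the group that then rules on the DSMC's recommendation already knows that the DSMC was worried. And the exercise of drafting two opposite conclusions works only while nobody involved can tell A from B. In a trial whose intervention is a visible reduction in fluid volume, a single table of fluids by arm could end that.

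**Working it through.** No planned sample size or power figure bears on this point. It rests on a comparison of sections, plus one calculation.

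**1. Steering group and authors**

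- Sections 5 and 5.4: the steering group and author group are blinded to allocation.
- Section 15.2: every principal site investigator is on the steering group. Section 11: its members are authors.
- Section 5.2.2: site investigators monitor adherence in both arms. The arms have different rules (5.2.1 against 5.2.2), so this cannot be done without knowing each patient's arm.
- Section 9.2: site investigators judge whether the intervention caused an event.

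The same people are thus described as blinded and given tasks that require the allocation. What they learn is limited to individual patients at their own site. It does not tell them which pooled group is labelled A.

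**2. Unblinding route**

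Appendix B section 6 addresses the request to the steering group, although the same section already provides an independent liaison who prepares the DSMC data so that trial personnel stay blinded. The request therefore reaches the decision-making body for no stated reason.

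**3. Would arm-coded fluid data reveal the code?**

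Input from section 2.4: the feasibility trial suggests that the approach may "reduce the total volume of administered fluids by a median of 3.6 (95% CI; 1.6 to 5.3) L" over the first 3 days.

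- Standard error, taking the estimate as roughly normal: SE = (5.3 − 1.6) / (2 × 1.96) = 3.7 / 3.92 = 0.944 L.
- Probability that the arm with less fluid is the intervention arm, for a true difference d: P = Φ(d / SE).
- d = 3.6 L: 3.6 / 0.944 = 3.81, P = 0.9999.
- d = 1.6 L (lower confidence limit): 1.6 / 0.944 = 1.70, P = 0.955.

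The feasibility trial's sample size is not given in the protocol, so the gain from a larger trial has to be assumed. With five times the information (SE / √5 = 0.422 L), P is 0.9999 at 1.6 L and 0.991 at 1.0 L.

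All of this is conditional on someone seeing fluid volumes by A and B. Section 6 gives the database to the coordinating team, and Appendix A shows that it holds daily non-resuscitation volumes and glucose strengths. The protocol states no order of analyses and names no separate handler for these data.

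**The case against.** The best reply is that section 5.4 describes a specific device: coded groups, two opposite conclusions, and approval before the code is broken. Knowing the arms of one's own patients does not defeat it. Interim comparisons are also shielded, because a liaison prepares the transfer (Appendix B section 6) and DSMC minutes stay within the DSMC (section 7). The primary outcome is all-cause mortality, which leaves little room for biased ascertainment. All of this stands. A reader might infer that the A/B safeguard gives no protection; the documents do not support that.

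A reader might also infer that the blind of the statisticians and coordinating team is bound to fail. That goes beyond the text too. No section says that they see fluid volumes by arm before the conclusions are fixed. Who performs central monitoring, and whether they see the arm, is not stated. The main paper reports primary and secondary outcomes (section 11), none of which is a fluid volume. A per-protocol set can be supplied as a yes/no flag, and the centre analysis as a list of centres. The order of data release may be set in the SAP, which is not at hand.

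Nor does Appendix B section 6 say that the steering group holds the code. It only makes that group the address for requests.

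These replies do not remove the conflict between sections 5 and 5.4 on one side and sections 15.2, 11, 5.2.2 and 9.2 on the other, or the misdirected request. An SAP that sequences the analyses would cure neither.

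**Conclusion.** The point holds in three parts of unequal strength.

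- **Contradiction on the page.** The unqualified blinding of the steering group and authors is not true of members with a site role. They can be blind to pooled results by arm and to the meaning of A and B, and to no more than that.
- **Weak procedure on the page.** DSMC unblinding requests go to the body that decides on DSMC recommendations, so the request itself carries information.
- **Inference.** The protocol does not keep arm-coded fluid or deviation data from those who analyse and approve the A/B conclusions. If a fluid table were seen, the code would very probably be known: about 0.955 at 1.6 L and 0.9999 at 3.6 L. This assumes feasibility-trial precision, an approximately normal estimate, and that the table is seen.

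Nothing here shows a failed blind for participants, the DSMC, the 6-month and one-year assessors or the statisticians; the DSMC file in Appendix B section 10 lists no fluid volumes. The likely effect on the mortality estimate is small. What is at stake is how interim decisions are made, how the results are interpreted, and whether the claim of blinding is accurate. It should be corrected, and the correction is cheap.

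**What to change.** 1. **Sections 1, 5 and 5.4.** State that steering group members and authors with a site role know individual allocations at their own site, and are blinded only to aggregate results by arm and to the A/B code. Leave the blinding statements for participants, the DSMC, the 6-month and one-year assessors and the statisticians as they are.
2. **Appendix B section 6.** Send DSMC unblinding requests to the independent liaison or the randomisation provider, not to the steering group.
3. **Section 11.** Analyse the primary and secondary outcomes under A/B and have both conclusions approved before fluid, glucose and deviation data by arm are released. Run the per-protocol and centre-separation analyses afterwards. If either is wanted earlier, supply it only as a yes/no flag or a list of centres. Name who holds the data back, since section 6 gives the database to the coordinating team.

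The cost is protocol and charter wording, a two-step data release with someone assigned to it, and slightly later per-protocol and centre analyses. No patients or trial procedures are affected.
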